#### Secondary outcomes

##### Social functioning

Personal and Social Performance Scale (PSP) [24]. An interview assessing the degree of disability (from 1, “absent”, to 5, “severe”) in four areas of social functioning: 1) socially meaningful activities (e.g., work, study); 2) personal and social relationships (e.g., friendships); 3) self-care (e.g., hygiene); and 4) disturbing and aggressive behavior (e.g., problems with law enforcement). The ratings for each domain are combined into one score from 0 (very low) to 100 (very high), which will be used for analysis.

##### Momentary mental states and social functioning in daily life

Experience Sampling Method (ESM) dairies are used to study the effects of the interventions on daily life interactions. An online questionnaire (21–33 items, included in Additional file 1: Table S1) is administered ten times a day for seven days at semi-random moments, by sending participants text messages containing a link to the questionnaire, which they can complete in the internet browser on a smartphone. Participants use their own smartphone or one provided by the research team. The ESM questionnaire assesses: 1) emotional state (positive and negative affect and stress level; thirteen items), on a visual analogue scale (VAS; 0–100); 2) current activities and activities since the last questionnaire (five items, to assess social and societal participation), selected from a multiple choice menu, and a VAS (0–100) on the enjoyability of the activity; 3) current social interactions and interactions since the last questionnaire (fourteen items), including the enjoyability of the interaction, feelings of being accepted, knowing how to respond, and feeling able to tell what the other person is feeling (VAS, 0–100); and 4) taking social initiative (two items; VAS, 0–100).

##### Psychiatric symptoms

The following measures of psychopathology will be administered, since (social) cognitive training may improve psychiatric symptoms, and symptom levels could be a moderator or mediator of treatment effect:
The Positive and Negative Syndrome Scale (PANSS) [25], a semi-structured interview assessing positive (7 items, range 7–49), negative (7 items, range 7–49) and general (16 items, range 16–112) symptoms of psychosis in the past week on a 7-point scale (from 1, “absent”, to 7, “very severe”). We will analyze the three subscales separately as well as the total score.The Social Interaction Anxiety Scale (SIAS) [26], a 20-item self-report questionnaire measuring verbal and non-verbal social anxiety on a 5-point Likert scale. We will analyze the total score.The Green Paranoid Thought Scale (GPTS) [27], a self-report questionnaire measuring paranoid thoughts of social reference ([16] items, part A) and social persecution (16 items, part B) in the past month on a 5-point Likert scale. We will analyze both subscales separately.Perceived Stress Scale (PSS) [28], a ten-item self-report questionnaire on symptoms of stress in the past week, indicated on a 5-point Likert scale. We will analyze the total score.

#### Other

##### Self-esteem

The Self-Esteem Rating Scale (SERS) [29]. The SERS is a twenty-item self-report questionnaire using a 7-point Likert scale, assessing feelings of self-worth and competence. Total scores will be analyzed.

##### Information processing and executive functioning

The Trailmaking Test (TMT) [30]. In TMT-A, participants connect numbers in circles scattered across a page in consecutive order; in TMT-B, participants connect numbers and letters in circles scattered across a page, alternating between the letters and circles in consecutive order (1-A-2-B, etc.). The completion time in seconds for both parts is analyzed.

##### Demographic and clinical background

Questions on different clinical and demographic variables, including: age, gender, handedness, eyesight, family history of psychiatric illness, education level of participant and participant’s parents, work history, diagnosis and illness duration (administered only at baseline); and housing status, employment status, substance use, medication use, hospitalizations and psychotic episodes (administered at each assessment).

##### Premorbid intelligence

The Dutch version (Nederlandse Leestest voor Volwassenen, NLV) [31] of the National Adult Reading Test [32]. Fifty increasingly uncommon words are read aloud by participants. Correct pronunciations are awarded a score of two points. The total score is used for analysis. The NLV is only administered at baseline.

##### Eligibility check

Mini International Neuropsychiatric Interview Plus (M.I.N.I.-plus) [18]. A structured clinical interview on symptoms of psychosis, depression and mania. The MINI-plus is administered at baseline to verify a diagnosis of psychotic disorder, if a diagnosis has not been determined by a structured clinical interview in the past three years.

#### Measures during treatment sessions

##### Cyber sickness

Simulator Sickness Questionnaire (SSQ) [33]. A self-report questionnaire on 27 common symptoms of simulator sickness (e.g., headache, nausea, dizziness), which will be administered right after the VR session 3 of both interventions to evaluate negative side effects of using VR. We will use the total score for analysis.

##### Performance and behavior during VR tasks

In the DiSCoVR group, the VR program will log several parameters during practice sessions (e.g., the avatars encountered, answers given to questions, time taken to answer, the number of answer attempts and interpersonal distance).

##### Emotions before and after relaxation

In the VRelax group, before and after each session in VR, participants complete a short questionnaire in which they rate their emotions (relaxed, anxious, gloomy, tranquil, stressed, excited, nervous and content) on a 0–100 VAS.

#### Assessment

The assessments are carried out by trained, independent research assistants. This study is single-blind, meaning that research assistants do not know to which intervention participants have been assigned. This is achieved by instructing coordinators, therapists and participants not to divulge group allocation to research assistants. Other precautions include storing data revealing group allocation (e.g., therapist worksheets) in a separate location and using different assistants for each measurement as much as possible. Blinding is evaluated with a self-report form for research assistants at the end of the post-treatment and follow-up assessments. We will perform a sensitivity analysis by testing the treatment effect only for measurements where research assistants reported being completely blinded to group allocation.

#### Randomization procedure

We utilized permuted block randomization with randomized block sizes (2, 4 or 6) using the R package ‘blockrand’ [34]. For each participating treatment center, we created strata for age (ten-year increments) and gender (i.e., ten strata per center). This resulted in a master randomization list with either ‘A’ or ‘B’ in each stratum. An independent employee then added an additional randomization by assigning DiSCoVR or VRelax to either A or B in the master randomization list using coin flips, once for each treatment center. Upon completing T_0_, the participants will be placed in the appropriate stratum in order of inclusion by the independent randomizer, determining their group assignment.

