## Methods/design

### Participants

Participants are recruited from Dutch mental health treatment centers (University Center of Psychiatry of the University Medical Center Groningen, GGZ Drenthe, GGZ Delfland, and Zeeuwse Gronden). We recruit participants in two ways: 1) through advertisement of the study, by distributing posters and flyers, allowing participants to enroll themselves; and 2) through clinician referral: clinicians refer eligible and interested participants. Inclusion criteria are:
A diagnosis of a psychotic disorder according to DSM-5 criteria, either determined by a structured clinical interview (e.g., Mini-international Neuropsychiatric Interview [18], Structured Clinical Interview for DSM [19], Schedules for Clinical Assessment in Neuropsychiatry [20]) in the past three years or verified using the MINI Plus at baseline.Deficits in social cognition, as indicated by a clinician.Age 18–65 years.

Exclusion criteria are:
(Photosensitive) Epilepsy.An estimated IQ below 70, and/or a diagnosis of intellectual disability.Insufficient proficiency in the Dutch language.

Participants receive a compensation of €30 for each completed assessment, up to a total of €90. They also receive reimbursement for travel expenses incurred for the assessments.

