#### Analysis

For our primary outcome variables (theory of mind and emotion perception), previous meta-analyses [6, 7] have found effect sizes ranging between moderate (*d =* .46, theory of mind) and large (*d* = .84, emotion perception). We therefore assumed a conservative effect size of .5. With β = .80, α = .05, two groups and three assessments, we found we would need 86 participants. Assuming a drop-out rate of 13% [35], we concluded that the sample should consist of 100 participants (50 in each group).

The groups will be compared at baseline using t-tests for normally distributed variables, and Mann-Whitney U-test or χ^2^ test for other variables. Variables with a significant baseline difference between the groups will be added to the analysis as a covariate.

We will use multilevel mixed-model linear regression analysis in accordance with the intention to treat principle, with repeated assessments (level 1) nested within participants (level 2). Time and group and their interaction term will be included as fixed effects. Treatment effects will be evaluated by examining the interaction between time and group. A random intercept will be included for the participant level to account for the repeated measures. A random slope will be included for time if this improves the model, according to the AIC value. The post-treatment and follow-up assessments will be analyzed separately, comparing each to the baseline. We will also perform a multilevel regression analysis on treatment completers, defined as people who have completed at least twelve sessions (75%) of their allocated intervention. Furthermore, moderator (e.g., clinical and demographic variables) and mediator analyses will also be conducted. Significance will be accepted at α = .05 (two-tailed); in case of multiple measurements within the same domain, a correction will be applied to α.

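### Forty randomisation strata for 100 participants leave most blocks unfilled, so balance by arm and centre is weaker than the blocking suggests

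*Protocol article*

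**What the plan says.** Protocol article, Randomization procedure: the scheme is "permuted block randomization with randomized block sizes (2, 4 or 6"). Within every treatment centre, "we created strata for age (ten-year increments) and gender (i.e., ten strata per center"). An independent employee then decided which of the labels A and B meant DiSCoVR, "using coin flips, once for each treatment center".

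Protocol article, Participants: the eligible range is "Age 18–65 years", and the centres are "University Center of Psychiatry of the University Medical Center Groningen, GGZ Drenthe, GGZ Delfland, and Zeeuwse Gronden".

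Protocol article, Analysis: on sample size, "we concluded that the sample should consist of 100 participants (50 in each group"). The mixed model has time, group and their interaction as fixed effects and a random intercept per participant. A covariate enters only if the arms differ significantly on it at baseline. Centre, age and gender are not named as model terms. Post-treatment and follow-up are each compared with baseline in a separate analysis, and the treatment effect is the time-by-group interaction.

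**The concern.** Permuted blocks balance the arms only when blocks are filled. A stratum that stops part-way through a block keeps whatever imbalance the open block had reached. With many small strata these remainders accumulate, and balance on the totals that matter most, overall and by centre, gets looser as strata are added.

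Centre matters here because both arms receive usual care, which may differ between sites. As described, the model does not routinely adjust for the factors used to stratify. The design thus allows more residual imbalance than a coarser scheme would, and the analysis does not take it up. What is at stake is precision and the credibility of within-centre balance.

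**Working it through.** **Inputs.** From the article: ages 18 to 65, two genders, four centres, blocks of 2, 4 or 6, and 100 participants allocated 1:1. Not in the article, so assumed: equal probability for the three block sizes, and the spread of recruitment over centres, ages and genders.

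**Number of strata.** 65 − 18 + 1 = 48 single years of age, which is five ten-year bands. 5 × 2 = 10 strata per centre, which reproduces the article's figure. 10 × 4 = 40 strata. 100 / 40 = 2.5 participants per stratum. Mean block size is (2 + 4 + 6) / 3 = 4.

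**Balance under the stated scheme.** Monte Carlo, 4,000 trials per scenario: 100 participants are spread over the 40 strata at random and allocated from blocks of 2, 4 or 6. The difference is the number in one arm minus the number in the other.

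- Equal: all shares equal.
- Skewed: centres .45/.25/.20/.10, age bands .20/.30/.25/.15/.10, genders .70/.30.
- More skewed: centres .60/.20/.15/.05, age bands .15/.35/.30/.15/.05, genders .75/.25.

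| Result | Equal | Skewed | More skewed | Simple randomisation |
|---|---|---|---|---|
| Strata with at least one participant | 36.8 | 31.6 | 26.3 | – |
| Strata with exactly one | 8.2 | 9.2 | 8.7 | – |
| Started blocks left unfilled | 67% | 62% | 55% | – |
| SD of overall difference | 6.1 | 5.8 | 5.2 | 10.0 |
| Chance of 55:45 or worse | 13.6% | 11.8% | 8.4% | 37% |
| Chance of 60:40 or worse | 0.2% | 0.08% | 0.02% | 5.8% |
| SD of difference within a centre | 3.1 | 2.5–3.1 | 1.9–3.1 | 2.2–7.8 (5.0 at n = 25) |

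Variance removed relative to simple randomisation: 1 − 6.14²/10² = 62% (equal) to 1 − 5.24²/10² = 73% (more skewed).

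**Coarser comparator.** Centre by gender gives 4 × 2 = 8 strata. With the same block sizes from the first participant, the overall SD is about 2.8, the within-centre SD about 1.4, the chance of 55:45 or worse about 0.1 to 0.3%, and about 21% of started blocks stay unfilled. In a centre of about 25, a difference of 6 or more occurs in about 7% of trials with 40 strata and essentially never with 8.

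**Power cost of unequal arms.** For a simple two-sample test with d = 0.5, power = Φ(0.5/√(1/n₁ + 1/n₂) − 1.96). At 50:50 this is Φ(2.500 − 1.960) = 70.5%. At 56:44 it is Φ(2.482 − 1.960) = 69.9%. Relative efficiency at 56:44 is 4 × 56 × 44 / 100² = 0.986. The 70.5% only measures the loss. It is not the power of the planned repeated-measures analysis.

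**Changing the scheme part-way.** The article does not say how many have been randomised, so the switch point was varied. SD of the overall difference after a switch to fresh centre-by-gender blocks, under equal / skewed shares (2,000 trials each):

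| Switch after | Overall SD |
|---|---|
| no switch | 6.1 / 5.6 |
| 25 | 5.1 / 4.9 |
| 40 | 5.6 / 5.8 |
| 50 | 5.9 / 5.8 |
| 60 | 6.5 / 5.8 |
| 80 | 6.6 / 6.0 |

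The open blocks are abandoned with their imbalance and new ones are started. Minimisation with a random element, on centre, gender and age and counting those already allocated, brings the overall SD to about 2 to 3 whether it starts after 0 or after 80 participants. It also improves balance by centre and age band.

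**The case against.** The strongest reply is that the scheme works. It removes 62 to 73% of the variance of the arm difference left by simple randomisation, and it also helps within centres (SD about 3 against 5 in a centre of 25). An open block can leave a difference of at most 3, and remainders from different strata partly cancel. All of that stands. A reader might infer that balance by arm and centre is largely lost; these figures do not support it.

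A reader might also infer a contradiction with the planned 50 per group. There is none: that figure is a sample-size target, and the count of ten strata per centre is arithmetically consistent.

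Nor does chance imbalance under valid randomisation bias the comparison. Therapist requirements differ between arms by design, so better centre balance could not remove that difference. Because the effect is read from change since baseline, stable differences in level between centres largely drop out. Only centre differences in change would matter, and the article gives no figure for them.

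What survives is the comparison with available alternatives. Against a coarser scheme using the same block sizes from the start, the five age bands roughly double the SD of imbalance, overall and within centre. The stated model does not compensate for this as a matter of routine.

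**Conclusion.** The point holds as a limited design weakness. The article fixes 40 strata for 100 participants. In every scenario tried, more than half of the started blocks stay unfilled (55 to 67%), the SD of the overall arm difference is about 5 to 6, and it is about 3 within a centre of 25. These SDs rest on assumed recruitment shares and equally likely block sizes; the stratum count does not.

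The count of 40 takes the article's ten strata per centre at face value, with bands starting at or near age 18. Calendar decades would give six bands and 48 strata, which does not match the text.

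Validity is not threatened, and the power loss from unequal arms alone is under one percentage point (0.6 points at 56:44). Harm from imbalance within centres cannot be quantified from the article. The point justifies an inexpensive correction in the analysis and, at most, a careful change to allocation.

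**What to change.** **(a) Analysis.** Pre-specify centre, gender and continuous age in the mixed model, regardless of any baseline significance test. Because the effect is the time-by-group interaction, enter them with their interactions with time: with complete data at two time points, a main effect of a fixed participant characteristic leaves that interaction estimate unchanged. Cost: 3 (centre) + 1 (gender) + 1 (age) = 5 parameters, and 5 more for the interactions with time in each two-time-point analysis. All three variables are already known at randomisation, so no new data are needed.

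**(b) Allocation, only if the list is changed at all.** For participants still to be randomised, use minimisation with a random element on centre, gender and age, carrying in all allocations already made and run by the same independent randomiser. Cost: a short amendment, and allocation computed participant by participant instead of read from a list.

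**(c) What to avoid.** Do not switch mid-trial to fresh centre-by-gender blocks. Once about half are randomised this brings little or no gain and gives up part of the age balance that the present scheme provides. That option suits only a trial that has not begun randomising.

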#### Protocol fidelity

Therapists in both conditions will complete an eight-hour training. Monthly group supervision, in which all ongoing cases are discussed, will be provided for both conditions, to aid therapists and improve protocol fidelity. Therapists who are unavailable for these meetings will receive individual supervision. A weekly consultation session with the research team will also be available. After each session, therapists will complete a session form, on which they indicate whether they completed all parts of the protocol for that session, and whether any anomalies occurred.

#### Drop-out

Participants will be able to discontinue the study at any point. They can also refuse participation in part of the study, such as the ESM questionnaires. For sensitivity analyses, participants will be considered treatment completers if they complete twelve sessions or more (> 75%). If participants drop out of treatment, they are asked to continue the assessments. If participants refuse or miss T_1_, they are still contacted for T_2_.

#### Data management

Participant data will be coded using a study ID. Personal information and informed consent will be stored separately to ensure anonymity. We will use an electronic case report form; paper source data will be stored securely at each respective location. An independent monitor, who performs yearly routine inspections, will be appointed to ensure study quality and integrity.

#### Analysis

For our primary outcome variables (theory of mind and emotion perception), previous meta-analyses [6, 7] have found effect sizes ranging between moderate (*d =* .46, theory of mind) and large (*d* = .84, emotion perception). We therefore assumed a conservative effect size of .5. With β = .80, α = .05, two groups and three assessments, we found we would need 86 participants. Assuming a drop-out rate of 13% [35], we concluded that the sample should consist of 100 participants (50 in each group).

The groups will be compared at baseline using t-tests for normally distributed variables, and Mann-Whitney U-test or χ^2^ test for other variables. Variables with a significant baseline difference between the groups will be added to the analysis as a covariate.

We will use multilevel mixed-model linear regression analysis in accordance with the intention to treat principle, with repeated assessments (level 1) nested within participants (level 2). Time and group and their interaction term will be included as fixed effects. Treatment effects will be evaluated by examining the interaction between time and group. A random intercept will be included for the participant level to account for the repeated measures. A random slope will be included for time if this improves the model, according to the AIC value. The post-treatment and follow-up assessments will be analyzed separately, comparing each to the baseline. We will also perform a multilevel regression analysis on treatment completers, defined as people who have completed at least twelve sessions (75%) of their allocated intervention. Furthermore, moderator (e.g., clinical and demographic variables) and mediator analyses will also be conducted. Significance will be accepted at α = .05 (two-tailed); in case of multiple measurements within the same domain, a correction will be applied to α.

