## Background

For many people who have a psychotic disorder, it is a challenge to have meaningful daily activities, such as work, and to develop and maintain personal and romantic relationships; many of them experience problems in social functioning [1]. To function in daily life, it is necessary to adequately handle social situations and to be able to interpret the emotions, thoughts, intentions and behaviors of other people. These capabilities are generally referred to as *social cognition.* However, in people with a psychotic disorder, deficits in social cognition are common; a meta-analysis found large deficits in emotion perception and processing, social perception and theory of mind, compared to healthy controls [2]. Deficits in these key domains have been found to be important, proximal predictors for social functioning [3]. Social cognition has therefore become a target for psychosocial interventions aiming to improve social functioning through social cognitive training [4], a class of interventions also known as social cognition training (SCT).

SCT aims to improve social cognition, and ultimately social functioning through repeated practice with social stimuli (e.g., identifying emotions in pictures of faces), and compensatory strategy training (e.g., verbalization of salient facial features) [5]. A meta-analysis [6] of all types of SCT found large effects on emotion perception (recognition of emotions), and small to moderate effects on theory of mind (the ability to recognize and reflect on others’ mental states). A more recent meta-analysis [7], including only comprehensive forms of SCT (i.e., targeting multiple areas of social cognition), found a large effect on emotion perception and theory of mind, and a small to moderate effect on attribution style (judgments about the causes of events and others’ behavior). Together, these meta-analyses suggest that it is possible to improve social cognition with SCT in people with a psychotic disorder.

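### The planning effect of .5 is labelled conservative but exceeds the protocol's own .46 for theory of mind; the 80% power is about 73% for the TASIT at that figure

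*Protocol article*

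**What the plan says.** The sample-size paragraph under Analysis in the protocol article refers to two meta-analyses that, for the primary outcome variables, "have found effect sizes ranging between moderate" (d = .46) and large (d = .84). The lower value is attached to theory of mind ("46, theory of mind") and the higher to emotion perception ("84, emotion perception"). The next sentence reads "We therefore assumed a conservative effect size of .5". The sample size follows: "With β = .80, α = .05, two groups and three assessments, we found we would need 86 participants". The β here is evidently meant as power. With 13% drop-out the target becomes 100, 50 per group. The same section sets a two-sided 5% level.

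The Abstract and Table 1 make the TASIT the primary measure of social perception and theory of mind, beside the Ekman 60 Faces for emotion perception. The Discussion hypothesises a benefit on both constructs.

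The Background describes the evidence in words. The meta-analysis of all types of training found "small to moderate effects on theory of mind"; the later one, limited to comprehensive training, found a large effect on theory of mind.

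**The concern.** A planning effect is conservative for an outcome only if it does not exceed the effect that the evidence supports for that outcome. The paragraph gives one figure for each primary construct, and .5 lies above one of them. The sample size is derived once, for both primary outcomes, and the article neither limits the 80% power to emotion perception nor argues separately for .5 on theory of mind.

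What is at stake is how a TASIT result is read. If the TASIT shows no difference, a reader who trusts the label will take it that an effect somewhat below the literature would have been detected with 80% probability. By the protocol's own lower figure, the probability is smaller.

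**Working it through.** **Inputs from the article (Analysis):** planning d = .5; cited d = .46 and .84; power .80; two-sided α = .05; two groups; three assessments; 86 evaluable; 13% drop-out; 100 enrolled.

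**Input not in the article:** the test used for the calculation and the within-person correlation ρ. Both are assumed in steps 1, 3 and 4; step 2 needs neither.

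**1. Reproducing the 86.** Take a between-group repeated-measures F test with f = d/2, noncentrality λ = f² × N × 3 / (1 + 2ρ), and 1 and N − 2 degrees of freedom. With ρ = .5 the divisor is 2.

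- d = .5: f = .25, λ = .0625 × 86 × 3 / 2 = 8.06, power 80.1%. The smallest even N reaching 80% is 86, as stated.
- Drop-out: 86 / .87 = 98.9, so 99, which the article rounds to 100.

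**2. Effect of .46 without assuming a correlation.** For a two-sided 5% test with 80% power at d = .5, the standardised effect is 1.960 + 0.842 = 2.802. It scales with d.

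- At .46: 2.802 × .46 / .5 = 2.577. Power = Φ(2.577 − 1.960) = Φ(0.617) = 73.2%.
- Required N grows by (.5 / .46)² = 1.18: 86 × 1.1815 = 101.6, so 102.

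**3. The same under the model of step 1 (ρ = .5).**

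| d | N assessed | λ | Power |
|---|---|---|---|
| .46 | 86 | .0529 × 86 × 3 / 2 = 6.82 | 73.3% |
| .46 | 100 | .0529 × 100 × 3 / 2 = 7.94 | 79.7% |
| .46 | 102 | .0529 × 102 × 3 / 2 = 8.09 | 80.4% |
| .84 | 86 | .1764 × 86 × 3 / 2 = 22.76 | 99.7% |

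**4. Range over the unstated correlation, N fixed at 86.**

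| ρ | Power at .5 | Power at .46 | N for 80% at .5 | N for 80% at .46 |
|---|---|---|---|---|
| .3 | 88% | 82% | 70 | 82 |
| .4 | 84% | 78% | 78 | 92 |
| .5 | 80% | 73% | 86 | 102 |
| .6 | 76% | 69% | 96 | 112 |
| .7 | 73% | 65% | 104 | 122 |

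Under this model only ρ of about .5 agrees with the stated 86. In every row, moving from .5 to .46 costs 6 to 7 points of power.

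**5. A different model as a check.** A baseline-adjusted comparison, with n per group = 2(1 − ρ²)(2.802 / d)², returns 86 in total when ρ is about .57: 2 × .6751 × 31.4 = 42.4, so 43 per group. At d = .46 it gives 2 × .6751 × 37.1 = 50.1, so 51 per group and again 102 in total.

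**The case against.** The strongest reply is that .46 is not the only theory-of-mind evidence in the article. The Background reports a large effect from the later meta-analysis of comprehensive training. DiSCoVR covers emotion perception, social perception, theory of mind and social interaction, so it fits that class, and the sample-size paragraph cites both meta-analyses. On that reading .5 sits between the weaker and the stronger estimate. This stands as mitigation: .46 is the low end of the evidence. It does not rescue the label, because the sample-size paragraph gives .46 as its theory-of-mind figure and offers no argument for going above it.

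A second reply is that power is conditional on the assumed effect, and at .5 the stated 86 is correct. That also stands. The fault is in the justification, and the sample-size calculation contains no arithmetic error.

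A third is that the loss is modest and may be smaller in practice. The plan enrols 100, analyses by intention to treat in a mixed model, asks those who stop treatment to continue assessments, and contacts those who miss post-treatment for follow-up. Partial data will contribute, so under the assumed model power at .46 would lie between 73.3% and 79.7%. This is fair, and it is why no change to enrolment is suggested.

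Two stronger readings are tempting:

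- A reader might infer that the TASIT comparison is underpowered outright. The article supports this only if .46 is the true effect, which its own Background leaves open.
- A reader might infer a larger shortfall because the planned test is the time-by-group interaction at each later assessment against baseline. That concerns which test was powered, depends on a correlation that the article does not give, and is separate from the choice between .5 and .46.

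**Conclusion.** The label is wrong for one of the two primary outcomes on the article's own figures. The 80% power with 86 evaluable participants holds at d = .5 and falls to about 73% at d = .46. That drop of about 7 points does not depend on the correlation; it follows from scaling a test that has 80% power at .5. The more specific figures (73.3% at 86, 79.7% at 100, 102 evaluable for 80%) rest on an assumed between-group repeated-measures F test with correlation .5. That model was chosen because it returns the stated 86; the article does not state it. Emotion perception at .84 is unaffected, with power above 99%. The contradiction is definite and the shortfall moderate.

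**What to change.** In the sample-size paragraph, delete the word *conservative*, or say that .5 is conservative only for emotion perception. Add that power for the TASIT at d = .46 is about 73% with 86 evaluable participants, and give the correlation assumed in the calculation. If the investigators regard .5 as reasonable for theory of mind because of the later meta-analysis of comprehensive training, they should say so there.

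The cost is one or two sentences and a less favourable stated power for the TASIT. Design, analysis and enrolment stay as they are.

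### The sample size of 86 rests on three assessments, but each planned test compares two; at the correlation that appears to lie behind 86, the planned test has about 63% power, not 80%

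*Protocol article*

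**What the plan says.** All of the relevant text is in the protocol article, section Analysis.

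- **Effect size.** The section cites meta-analytic effects of d = .46 for theory of mind and .84 for emotion perception, then states: "We therefore assumed a conservative effect size of .5".
- **Error rates.** "With β = .80, α = .05". The .80 can only be meant as power. Testing is two-tailed at .05.
- **Result.** "two groups and three assessments, we found we would need 86 participants". This is raised to 100, 50 per group, for 13% drop-out.
- **Planned test.** "Treatment effects will be evaluated by examining the interaction between time and group".
- **Planned contrasts.** "The post-treatment and follow-up assessments will be analyzed separately, comparing each to the baseline".

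The section does not say which test was powered or what correlation between assessments was assumed.

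**The concern.** The sizing and the analysis describe different tests. A calculation that takes three assessments as an input is not a calculation for a contrast of one later assessment with baseline.

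The difference matters because repeated assessments affect the two kinds of test in opposite ways. In a between-groups main effect, extra assessments are averaged, which reduces variance, and a lower correlation helps. In a change from baseline, the baseline score is subtracted, which adds variance unless the correlation is high, so a lower correlation hurts. A main effect over all three assessments also counts the group difference at T0. The section Randomization procedure places allocation after T0 is completed, so that difference is zero in expectation.

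Both primary outcomes (Ekman 60 Faces and TASIT part III) are to be judged by these contrasts. If their power is well below 80%, a null result read against the stated power would be taken as stronger evidence of no effect than it is.

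**Working it through.** **Inputs from the article:** d = .5 (f = .25 for two equal groups), two-sided α = .05, power .80, two groups, three assessments, N = 86, 13% drop-out, 100 enrolled.

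**Input not in the article:** the correlation ρ between assessments. It is taken as .5, with a range shown, and assumed equal for all pairs of assessments, with equal variances.

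**1. Reproducing 86.** For a between-groups main effect over m assessments, with 1 and N − 2 degrees of freedom, the noncentrality is

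λ = f² · N · m / [1 + (m − 1)ρ].

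With m = 3 and ρ = .5, λ = .0625 × 86 × 3 / 2 = 8.06, and power is 80.1%. At N = 84, λ = 7.88 and power is 79.2%. So 86 is the smallest even N that reaches 80%. The drop-out step also reproduces: 86 / .87 = 98.9, so 99, stated as 100.

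Other tests at ρ = .5 give different totals:

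| Test at ρ = .5 | N for 80% power |
|---|---|
| Between-groups main effect, m = 3, f = .25 | 86 |
| Interaction, m = 3, f = .25 | 28 |
| Interaction, m = 3, f = .125 | 106 |
| Baseline-adjusted comparison of one later score | 98 |
| Mean of T1 and T2 minus T0 | 98 |
| Two-sample t-test on one score | 128 |

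**2. The planned contrast.** With two assessments and complete data, the time-by-group interaction is a comparison of mean change between groups. In units of the raw SD, the SD of change is √[2(1 − ρ)], so

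noncentrality = d / √[2(1 − ρ)] × √(N/4), with N − 2 degrees of freedom.

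At ρ = .5 the SD of change is 1. With N = 86 the noncentrality is .5 × √21.5 = 2.32 and power is 63%. With N = 100 it is .5 × 5 = 2.50 and power is 70%.

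| ρ | Power, N = 86 | Power, N = 100 | N analysed for 80% |
|---|---|---|---|
| .3 | 49% | 55% | 178 |
| .4 | 55% | 62% | 154 |
| .5 | 63% | 70% | 128 |
| .6 | 73% | 79% | 104 |
| .67 | 80.5% | 86% | 86 |
| .7 | 84% | 89% | 78 |
| .8 | 95% | 97% | 54 |

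At ρ = .5, 128 analysed means 128 / .87 = 147.1, so 148 enrolled at 13% drop-out.

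**3. The main-effect test under a realistic pattern.** If the group difference is 0 at T0 and .5 at T1 and T2, its average is (0 + .5 + .5)/3 = .333. The SD of a mean of three scores at ρ = .5 is √[(1 + 2 × .5)/3] = .816. The noncentrality at N = 86 is (.333/.816) × √21.5 = 1.89, and power is 46%. So the test that appears to have been used would not have 80% power either once the baseline difference is zero.

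**4. Lower source effect.** At d = .46 and ρ = .5, the planned contrast has 56% power with N = 86.

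**5. Baseline-adjusted comparison.** The residual SD is √(1 − ρ²) = .866 at ρ = .5. The noncentrality is (.5/.866) × √(N/4): 2.68 at N = 86 (power 75%) and 2.89 at N = 100 (82%).

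**The case against.** A reader might infer from the exact match that the article powered a group main effect, and that 80% power is therefore simply not delivered. The documents support neither statement outright.

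- **Origin of 86.** The article names no test and no correlation. 86 also results from the planned change contrast at ρ of about .67, from a baseline-adjusted comparison at about .58, and from the mean of T1 and T2 minus T0, which does use three assessments, at about .56. This objection stands: the main-effect origin is inferred. The round value .5 makes it the likeliest, and none of the alternatives both uses three assessments and matches the planned separate contrasts.
- **Size of the shortfall.** The article gives no test-retest correlation for either primary outcome, so it does not show that the true value lies below .67. This also stands; above that value 86 is enough.
- **Analysed number.** The section Drop-out asks those who stop treatment to continue assessments, and those who miss T1 are still contacted for T2. The analysed number may lie between 86 and 100, which gives 63% to 70% at ρ = .5.
- **The two outcomes differ.** If the cited d = .84 holds for emotion perception, the planned contrast has 97% power at ρ = .5 and N = 86. The risk then falls mainly on theory of mind.
- **Condensation.** An article may leave the powered test and the correlation to the full protocol or the SAP, so their absence is not itself a fault. The conflict between three assessments in the sizing and two per test remains, because both are printed in the same section.

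**Conclusion.** The point holds in a qualified form. The mismatch between the sizing and the planned tests can be read directly from the text, and confidence in it is high. That 86 came from a between-groups main effect with ρ = .5 is an inference held with moderate confidence.

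Under d = .5, two-sided α = .05, equal correlations and ρ = .5, each planned contrast has about 63% power with 86 analysed and 70% with 100, against a stated 80%. The shortfall disappears at N = 86 if the correlation with baseline is about .67 or higher, and it widens below .5. The stated 80% is thus not established for the tests to be run, which is a weaker statement than saying it is missed. This should be fixed. It does not undermine the trial's design.

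**What to change.** In the sample-size paragraph and the SAP:

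1. State the power for the T1–T0 and T2–T0 group differences in change, giving the assumed correlation with baseline and a range. For example, at d = .5 and 86 analysed: 55% at .4, 63% at .5, 73% at .6 and 84% at .7, with 70% at .5 if all 100 contribute.
2. Stop giving three assessments as the basis of the calculation.
3. Write power = .80 in place of β = .80.
4. Keep N = 100.

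Optionally, analyse each later assessment with adjustment for its baseline score. At ρ = .5 this gives about 75% power with 86 and 82% with 100, and so recovers most of the loss.

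The first four changes cost only wording and a less favourable power statement; no extra participants are needed. The optional one changes the primary model and would have to be fixed before the data are unblinded.
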